### Sample size and duration of the study

2.4

Each year, approximately 180–200 rectal cancer patients receive NACTRT at our hospital, with approximately 70% undergoing surgery and 15%–20% developing progressive disease. The current pCR rate at our hospital following NACTRT is approximately 15%, while the literature indicates a pCR rate of 25%–30% with statin therapy. We hypothesize that rosuvastatin can increase the pCR rate by 10%, from 15% to 25%. To detect a 10% difference in pCR rates, with a two-sided alpha of 0.10 and 80% power, a sample size of 288 patients would be required. Factoring in a 10% attrition rate, the total sample size increases to 316. Approximately 500–600 patients will need to be screened to enroll 316 participants. It is estimated that accrual and analysis will take approximately 3 years to complete.

A follow-on phase III trial is also will be planned depending on the success of the phase II study, which will compare the 3-year DFS in the two arms. All the patients in the phase II study will be included in the survival statistics in the follow-on phase III study which will be statistically powered for survival. Assuming that the addition of rosuvastatin to NACTRT will improve the 3-year DFS from 60% to 67%, our calculated sample size will be 1,135 subjects (567 in the control group and 568 in the treatment group) (a two-sided log-rank test with 80.0% power at a 0.050 significance level). This assumes a uniform accrual pattern across time periods and 10% dropout rate. If we move on to the phase III study, another 4 years will be required for accrual. The total duration will be 7 years for accrual and 3 years for follow up.

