**Methods:**

This is a prospective, randomized, open-label phase II/III study. The phase II study has a sample size of 316 patients (158 in each arm) to be accrued over 3 years to have 288 evaluable patients. The standard arm will receive NACTRT while the intervention group will receive 20 mg rosuvastatin orally once daily along with NACTRT for 6 weeks followed by rosuvastatin alone for 6–10 weeks until surgery. All patients will be reviewed after repeat imaging by a multidisciplinary tumor board at 12–16 weeks after starting NACTRT and operable patients will be planned for surgery. The pathological response rate, tumor regression grade (TRG), and post-surgical complications will be recorded.

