#### Randomization

2.3.3

Patients will be randomized in a 1:1 ratio using block randomization to rosuvastatin and NACTRT or NACTRT alone. An independent statistician will generate the randomization code and independent research staff will inform the study team of the allocation. A randomization log will be maintained by the study team.

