### Statistical analysis

2.6

Quantitative data will be presented as mean ± SD and categorical variables as frequencies within each cohort. The comparison of the statin and non-statin groups will be done using Fisher’s exact test or a χ2 test for categorical variables, and a Wilcoxon rank sum test for quantitative variables. Univariate analysis of significant predictors of an AJCC grade 0 response to NACTRT will be performed by a χ2 or Fisher’s exact test for categorical variables and logistic regression for quantitative variables. Multivariate analysis of statin use as a predictor of AJCC grade 0 responses to NACTRT will be done using multivariable logistic regression models. A Kaplan–Meier survival analysis will be used to determine the effect of statin use and AJCC TRG score on overall survival and disease-free survival. Cox proportional hazard models will be used to determine whether statin use was a significant predictor of recurrence and survival outcomes after adjusting for predicted covariates. All secondary endpoint comparisons will be made using the two-sided log-rank test with a 0.05 significance level. Assuming that OS demonstrates significance in the phase II study, the same criteria would be used for the analysis of PFS. For potential prognostic and predictive factors, multivariate analysis would be performed based on gender, metastasis occurrence from accrual to follow-up timepoint, histology subtype (diffuse, intestinal), and measurable disease (yes, no).

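### The phase II sample size of 288 gives 80% power only at a one-sided alpha of 0.10; at the stated two-sided 0.10 the power is about 68%

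*Protocol article*

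**What the plan says.** Section 2.4 (Sample size and duration of the study) sets the phase II hypothesis as a 10-point rise in pCR, from 15% to 25%, and states that "with a two-sided alpha of 0.10 and 80% power, a sample size of 288 patients would be required". It then adds 10% for attrition to reach 316. The Abstract (Methods) repeats the numbers: "316 patients (158 in each arm) to be accrued over 3 years to have 288 evaluable patients". Allocation is 1:1 (section 2.3.3: "Patients will be randomized in a 1:1 ratio using block randomization"). No section gives a one-sided alpha for the pCR comparison.

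Section 2.6 (Statistical analysis) begins its description of the arm comparison with "The comparison of the statin and non-statin groups will be done using" and then allows either Fisher's exact test or a chi-square test for categorical variables. It does not say which applies to pCR.

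Sections 1.3 and 2.4 make the move to phase III conditional on a positive or successful phase II. Section 2.1 describes the decision as resting on feasibility, safety and efficacy.

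**The concern.** Section 2.4 fixes the control rate, the effect, alpha, its sidedness, power and N together, so any one of them can be checked against the rest. A total of 288 is small for a 15% versus 25% comparison at two-sided 0.10.

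If N is too small for the stated rule, the primary analysis has materially less power than claimed, and a null result would be read with more confidence than it deserves. If the rule actually intended is one-sided 0.10, the chance of falsely declaring benefit is 10%, not the 5% that two-sided 0.10 implies in that direction. Either way, the threshold for a positive primary result is ambiguous, and that result feeds the phase III decision.

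**Working it through.** **Inputs (protocol article).** p1 = 0.15, p2 = 0.25, difference 0.10, alpha 0.10 two-sided, power 80% (section 2.4); 1:1 allocation (section 2.3.3); 288 evaluable, so 144 per arm (Abstract and section 2.4).

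**Formula.** Pooled-variance normal approximation for two proportions, with mean rate 0.20:

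n per arm = [z_a·√(2 × 0.20 × 0.80) + z_b·√(0.15 × 0.85 + 0.25 × 0.75)]² / 0.10²

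Here √0.32 = 0.5657, √(0.1275 + 0.1875) = √0.315 = 0.5612, and z_b = 0.8416 for 80% power.

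**Reproducing the plan's figure.** With z_a = 1.2816 (one-sided 0.10, the same as two-sided 0.20):

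n = (0.7250 + 0.4723)² / 0.01 = 143.4, rounded up to 144 per arm = **288**, an exact match.

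**The stated rule.** With z_a = 1.645 (two-sided 0.10):

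n = (0.9305 + 0.4723)² / 0.01 = 196.8, rounded up to 197 per arm = **394**, which is 106 more than stated.

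**Could another formula give 288 at two-sided 0.10?** No:

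| Version | Total N, two-sided 0.10 | Total N, one-sided 0.10 |
|---|---|---|
| Pooled | 394 | 288 |
| Unpooled | 390 | 284 |
| Mean rate only | 396 | 290 |
| Arcsine | 392 | 286 |
| Continuity-corrected | 434 | 326 |

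**Power at 144 per arm, two-sided 0.10.**

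z = (0.10 × √144 − 1.645 × 0.5657) / 0.5612 = (1.2000 − 0.9305) / 0.5612 = 0.480, so power is **68.4%**.

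| Method | 144 per arm, two-sided 0.10 | 144 per arm, one-sided 0.10 | 158 per arm, two-sided 0.10 |
|---|---|---|---|
| Normal approximation, pooled | 68.4% | 80.1% | 72.0% |
| Exact enumeration, uncorrected chi-square | 69.1% | 80.7% | 72.3% |
| Exact enumeration, Fisher's exact | 63.3% | 76.1% | 67.6% |

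The last column shows that the attrition allowance does not close the gap, even if all 316 patients were evaluable.

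**Detectable difference.** With 144 per arm, two-sided 0.10 and 80% power, solving the same formula from a 15% control rate gives about 11.9 points.

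**Observed difference needed for significance.** With an observed control rate of 15% and 144 per arm, solve d = z_a·√[2·p(1 − p)/144], where p = 0.15 + d/2:
- two-sided 0.10: d ≈ 7.6 points
- one-sided 0.10: d ≈ 5.8 points

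An observed difference between these values is positive under one reading and negative under the other.

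**The case against.** The arithmetic is not open to dispute. The fair objections concern what is built on it.

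- **The origin of the error is inferred.** The exact match at one-sided 0.10 is strong evidence of a sidedness mislabel, but the document does not say so. This stands, and only the original calculation record could settle it. The inconsistency does not depend on the explanation.
- **Type I error is not inflated in every sense.** A one-sided 0.10 test has a total type I error of 0.10, numerically the stated value. This stands. What doubles is the chance of a false claim of benefit (5% to 10%), or equivalently the two-sided alpha (0.10 to 0.20).
- **The choice of test is a generic sentence** and could be settled in an analysis plan that is not shown. This stands in part: the point is secondary, and the main finding holds without it. It still costs about 6 points of power here (69% versus 63%).
- **Phase III does not rest on the pCR test alone.** Correct. Section 2.1 also lists feasibility and safety. Efficacy remains one of the three criteria, and pCR is the primary efficacy variable.
- **The trial may still be adequate for a larger effect.** Section 2.4 cites pCR rates of 25% to 30% with statins. For 15% versus 30%, power at 144 per arm and two-sided 0.10 is about 92%. That is true, but the design hypothesis is 25%, and the 80% claim is made for that.

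**Conclusion.** The concern holds. For 15% versus 25% with 144 evaluable patients per arm, power at the stated two-sided 0.10 is about 68% by the standard formula, and ranges from 63% (Fisher) to 69% (chi-square) by exact enumeration. The type II error is therefore roughly 31% to 37%, not 20%. The stated alpha and power together need 394 evaluable patients; 288 matches one-sided 0.10 exactly. This is a wrong statement about the primary endpoint rather than an omission, so an analysis plan that repeated it would carry the same error.

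The result assumes the protocol's own pCR rates, equal arms and full delivery of the 288 evaluable patients. Fewer evaluable patients would lower power further.

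**What to change.** Correct the statement in section 2.4 and keep N, choosing one of:

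- **(a)** phase II is tested at one-sided alpha 0.10 (equivalent to two-sided 0.20), with 80% power for 15% versus 25%; or
- **(b)** phase II is tested at two-sided alpha 0.10, with power of about 68% for 15% versus 25%, and 80% only for a difference of about 12 points.

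In section 2.6, name one primary test for pCR. The uncorrected chi-square test fits the sample size formula, so remove the Fisher alternative for this endpoint. Define a positive phase II efficacy result by the same test and alpha.

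Option (a) lowers the bar for success from about 7.6 to about 5.8 points. The choice should therefore be made and dated without sight of outcome data and, if possible, supported by the original calculation record.

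The cost is wording in sections 2.4 and 2.6 and a less favourable stated alpha or power; no extra patients are needed. The only way to keep two-sided 0.10 and 80% power together is to enlarge the trial to 394 evaluable patients, about 438 enrolled at 10% attrition (394 / 0.90 = 437.8).

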#### Study specific investigations

2.3.8

All investigations will be done as per the current standard of care. There will be no additional planned blood tests or imaging done for the purpose of the study. In patients who agree to participate in the molecular sub-study, the baseline samples will be taken at the time of the baseline endoscopy and post-treatment samples for the operated patients will be from the resected specimen. Post-treatment samples for patients who are not operated on (approximately 30% of those receiving NACTRT) will be collected by conducting a repeat limited sigmoidoscopy. The patients will be reimbursed for this and the same is mentioned in the ICF as well. The follow-up will be as per the prevailing standard of care.

The schedule of events are depicted in **Table 3**.

**Table 3 T4:** Schedule of events.

	Baseline	Randomization	Week 2 visit ±3 days	Week 4 visit ± 3days	Week 6 and 7 visit ±3 days	Week 12 visit ±3 Days	Week 14 to 16 visit ±3 days
Informed Consent	✓						
Screening of patients with biopsy-confirmed adenocarcinoma of the rectum	✓						
Collection of four additional tissue samples for molecular sub-study	✓						
Collection of 7–8 ml of blood	✓						
Randomization		✓					
Both arms NACTRT			✓	✓	✓		
Statin dispensed		✓			✓		**
Statin pill counts			✓	✓	✓		✓
Adverse event/serious adverse event reporting			✓	✓	✓	✓	✓
Clinical review			✓	✓	✓	✓	✓
Radiological review						✓*	✓*
MDTB decision for surgery							✓
Collection of four additional tissue sample post-surgery							✓#

*Radiological assessment will be done at 6–8 weeks after completion of NACTRT.

**Rosuvastatin will be stopped a day prior to surgery (operable patients) or on the day deemed inoperable (inoperable patients).

#Paired tissue samples will be collected from patients who are operated on via the resected specimen (post-treatment sample) or fresh biopsies for patients who are not operated on.

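### The step from 288 evaluable to 316 enrolled is slightly miscalculated, and the 10% attrition allowance is not reconciled with about 30% of patients going unoperated or with three conflicting analysis populations

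*Protocol article*

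**What the plan says.** Section 2.4 sets the phase II target: "We hypothesize that rosuvastatin can increase the pCR rate by 10%, from 15% to 25" per cent, "with a two-sided alpha of 0.10 and 80% power, a sample size of 288 patients would be required". It continues: "Factoring in a 10% attrition rate, the total sample size increases to 316". The abstract repeats this as "316 patients (158 in each arm) to be accrued over 3 years to have 288 evaluable patients".

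On patient flow, section 2.4 describes the hospital's NACTRT patients "with approximately 70% undergoing surgery and 15%–20% developing progressive disease". Section 2.3.8 agrees, referring to "patients who are not operated on (approximately 30% of those receiving NACTRT").

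Three sections bear on who enters the pCR analysis:

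- Section 2.5 (Statistical consideration) defines the primary variable on resected specimens, in patients who have surgery.
- Section 2.3.6 (Assessment of response) treats patients whose disease is inoperable at reassessment as non-responders and analyses them with the non-pCR group.
- Section 2.3.9 (Withdrawal/stopping criteria) leaves out of the phase II analysis patients who responded but were not operated on.

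No section says what the 10% attrition covers, which of these populations the 288 refers to, or whether the 15% planning rate is per resected or per treated patient.

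**The concern.** There are two separate issues.

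The first is arithmetic. To keep a target after a fractional loss, divide by the fraction retained. Multiplying by one plus the loss falls short.

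The second matters more. pCR can be observed only in a resected specimen, and the protocol expects about 30% of patients not to be resected. Whether those patients are lost to the primary analysis or kept as failures decides both the evaluable number and the pCR rate to plan on. The three sections give different answers, and a 10% allowance does not obviously follow from any of them. The evaluable number promised in the abstract, and the power resting on it, therefore cannot be checked against the plan.

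**Working it through.** **Inputs.** Rates of 15% and 25%, 80% power, two-sided alpha 0.10, 288 evaluable, 10% attrition, 316 enrolled, about 70% operated and 15–20% progressing (all section 2.4); about 30% not operated on (2.3.8); 1:1 allocation (2.3.3).

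**Step 1: reproduce 288.** Per arm, with the pooled-variance formula, n = [z_α √(2·0.20·0.80) + 0.8416 √(0.15·0.85 + 0.25·0.75)]² / 0.10².

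- One-sided 0.10 (z = 1.2816): (0.7250 + 0.4723)²/0.01 = 143.4, so 144 per arm and 288 in total.
- Two-sided 0.10 (z = 1.6449): (0.9305 + 0.4723)²/0.01 = 196.8, so 197 per arm and 394 in total.

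The plan's 288 matches a one-sided alpha, not the stated two-sided one. That is a separate error. It matters here because power must be shown under both alphas to isolate what attrition does.

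**Step 2: reproduce 316.** 288 × 1.10 = 316.8; per arm 144 × 1.10 = 158.4, cut to 158, giving 316. The correct inflation is 288/0.90 = 320. In the other direction, 316 × 0.90 = 284.4. The loss at which 316 still yields 288 is 1 − 288/316 = 8.9%, or 28 patients.

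**Step 3: evaluable patients under each rule.**

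- Operated patients only (2.5): 316 × 0.70 = 221.2. Reaching 288 would need 288/0.70, or 412 enrolled.
- Inoperable patients kept, unoperated responders excluded (2.3.6 with 2.3.9): the loss is the number of unoperated responders, which is not given. Assumption: patients with progression are all unoperated and kept as non-pCR, and every other unoperated patient is excluded. The loss is then 30% − 20% = 10% to 30% − 15% = 15%, leaving 284.4 to 268.6. Reaching 288 would need 320 to 339 enrolled.

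**Step 4: power for 15% versus 25%.** Power = Φ[(0.10 − z_α·√(0.20·0.80·2/n)) / √((0.1275 + 0.1875)/n)], with n per arm equal to half the evaluable total.

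| Evaluable | One-sided 0.10 | Loss against 288 | Two-sided 0.10 | Loss against 288 |
|---|---|---|---|---|
| 288 (as stated) | 0.8013 | – | 0.6845 | – |
| 284 (10% loss) | 0.7972 | 0.4 points | 0.6792 | 0.5 points |
| 269 (15% loss) | 0.7807 | 2.1 points | 0.6585 | 2.6 points |
| 221 (operated only) | 0.7195 | 8.2 points | 0.5852 | 9.9 points |

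**Step 5: the denominator of the 15%.** Suppose all 316 are analysed and unoperated patients count as non-pCR. If 15% and 25% are rates among resected patients (assumption), with 70% resected in each arm, the rates become 0.70 × 15% = 10.5% and 0.70 × 25% = 17.5%. With 158 per arm, power is 0.5592 two-sided or 0.6964 one-sided. If 15% and 25% already refer to all treated patients, power with 316 is 0.7196 two-sided or 0.8284 one-sided.

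**The case against.** The inflation slip is four patients in 320, or 1.3%, and on its own would not merit more than a correction. That stands.

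A reader might infer that 288 evaluable patients cannot be reached on any reading. The protocol does not support that. Section 2.3.6 keeps inoperable patients in the analysis, so being unoperated is not the same as being lost. Section 2.3.9 excludes only responders without surgery, and their number is not given. If that group and all other losses stay at or below 8.9%, 288 is met.

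A reader might also infer that the protocol's figures imply a loss above 10%. That is not established either. The 10–15% in step 3 treats progression and surgery as mutually exclusive and every remaining unoperated patient as an excluded responder. Patients inoperable without progression would stay in as non-pCR and lower the loss. The 70% and 15–20% also describe the hospital's NACTRT patients in general, not the trial's selected population. Nor does section 2.3.9 say that withdrawn patients leave the analysis, so withdrawals cannot simply be added as further loss.

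Finally, power of 66–68% at two-sided 0.10 could be blamed on attrition. Most of that gap from 80% is already there with all 288 patients, which give only 68%.

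It can also be said that section 2.5 merely describes the variable while section 2.3.6 settles the population. That is a fair reading, but the text does not say so, and section 2.3.9 adds a third rule. The inconsistency remains.

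**Conclusion.** The concern holds in a limited form. As written, 316 enrolled with 10% attrition gives about 284 evaluable, not 288; this is a real but small error, worth 0.4 to 0.5 points of power.

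The substantive defect is that the 10% allowance is tied neither to the expected 30% unoperated nor to a single analysis population. Its size depends on the rule chosen. Under the section 2.5 wording, about 221 patients are evaluable and power drops by 8 to 10 points: from 80% to 72% one-sided, or from 68% to 59% two-sided. Under sections 2.3.6 and 2.3.9 the loss is undetermined. On the assumption in step 3, 269 to 284 patients remain, with power of 78–80% one-sided or 66–68% two-sided, a cost of at most about 2.6 points.

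Analysing everyone randomised does not by itself secure power. If the planning rates are per resected patient, dilution leaves about 56% two-sided or 70% one-sided.

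**What to change.** 1. Define one primary analysis population and use it in sections 2.3.6, 2.3.9 and 2.5. The preferable choice is all randomised patients, with a stated pCR classification for each type of patient not operated on (inoperable, progressed, responder without surgery, withdrawn).
2. State in section 2.4 whether the 15% is per resected or per treated patient, and express both planning rates on the denominator the endpoint uses. If they are per resected patient and unoperated patients count as non-pCR, report the diluted rates (about 10.5% versus 17.5%) and the resulting power.
3. Restate the evaluable number and power in section 2.4 and the abstract. If 316 and 10% attrition are kept, the evaluable figure is 284; if 288 is kept, enrolment is 320. If only operated patients are analysed, the figures are about 221 evaluable from 316, or 412 enrolled for 288.
4. Give power under the alpha actually intended, so that the effect of attrition is not confused with the mismatch between 288 and two-sided 0.10.

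These are text changes. Analysing all randomised patients needs no extra enrolment to remove the evaluability loss, but it does not make up for dilution of the rates.

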### Statistical consideration

2.5

A) The primary efficacy variable is a pathological complete response which is defined as the absence of microscopic tumors in the resected specimens in patients who undergo surgery following neoadjuvant chemoradiotherapy.

B) The secondary efficacy variables are toxicity and 3-year DFS.

C) Toxicity will be assessed as detailed below. The NCI Common Terminology Criteria for Adverse Events version 4 (NCI CTCAE v4.03) will be used to classify and grade the intensity of adverse events during and after chemo-radiotherapy. The worst grade of each toxicity episode will be recorded. All events regardless of attribution will be graded so as to ensure objectivity in reporting as per accepted international guidelines. The details will be entered in the dataset.

D) Any adverse event that occurs from the day of randomization until the end of study visit will be defined as an acute adverse event. Events that occur thereafter will be defined as chronic adverse events. Both acute and chronic adverse events will be recorded however only events happening till 30 days after surgery will be reported and not beyond.

E) Postoperative morbidity and mortality will be any event occurring from the day of surgery until 30 days.

F) Disease-free survival is defined as the time from the date of randomization until the date of disease recurrence or until death from any cause.

G) Progression-free survival (PFS) is defined as the time from the date of randomization until the date of disease recurrence or until death from any cause. If there is a clinical suspicion of progression, further workup and management will be as per the institutional standard. Progression will be assessed by the investigator using appropriate workup and investigations, as per routine care.

H) Overall survival is defined as the time from the date of randomization until the date of death from any cause.

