#### Assessment of response

2.3.6

Clinical and radiological assessment will be done at 6–8 weeks after completion of NACTRT. Eligible patients will undergo standard surgery (anterior resection, abdominoperineal resection, inter-sphincteric resection, or multi-visceral resection) according to the level and extent of growth. If the reassessment MRI at 12–14 weeks after completion of NACTRT shows inoperable disease, then the patient will be deemed a non-responder and analyzed as part of the non-pCR group. These patients, if on the rosuvastatin arm, will stop the statin on the day they are deemed inoperable by the MDTB. These patients will receive further chemotherapy to downstage the disease as per the current standard of care. A histopathological examination will be conducted for the patients operated on and the pathological response rate and tumor regression grade (TRG) will be judged according to the American Joint Committee on Cancer (AJCC) (**Appendix 1** in **Supplementary Material**). A pCR is defined as no residual cancer found on histological examination of the TME specimen (Grade 0 AJCC or Grade 1 Mandard’s). The pathologist assessing the specimen will be blinded to the treatment that the patient received.

Following surgery and the availability of the histopathology report, the patient would have completed the active phase of the study and will be followed up according to standard follow-up protocol. Survival details will be collected at each follow-up visit or telephonically if the patient misses a visit for any reason.

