#### Withdrawal/stopping criteria

2.3.9

The patient will be withdrawn from the study if:

The patient develops unacceptable toxicity.If the patient wishes to withdraw from participation.There is a need for a dose reduction of more than 1 level or discontinuation of the study drug.The patient does not comply with the protocol.

Patients who are not operated on despite a response will not be analyzed in the phase II study but will be followed up for survival and included in the analysis of the phase III study if it is conducted.

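### The primary endpoint is worded for operated patients only, while another section counts inoperable patients as non-pCR, so the pCR denominator is not fixed

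*Protocol article*

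**What the plan says.** Four places in the protocol article bear on who counts in the primary analysis.

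- **Section 2.5, item A** gives the primary efficacy variable as "absence of microscopic tumors in the resected specimens in patients who undergo surgery following neoadjuvant chemoradiotherapy".
- **Section 2.3.6** also ties pCR to a specimen: "A pCR is defined as no residual cancer found on histological examination of the TME specimen". In the same paragraph it deals with patients whose reassessment MRI shows inoperable disease: "then the patient will be deemed a non-responder and analyzed as part of the non-pCR group".
- **Section 2.3.9** removes a third group: "Patients who are not operated on despite a response will not be analyzed in the phase II study". They are kept for survival follow-up and for phase III.
- **Section 2.4** describes the hospital's own patients, "with approximately 70% undergoing surgery and 15%–20% developing progressive disease". Section 2.3.8 agrees, referring to "patients who are not operated on (approximately 30% of those receiving NACTRT").

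Section 2.4 plans for pCR rates of 15% and 25% without saying whether these are rates among operated patients or among all treated patients. It asks for 288 patients, raised to 316 for 10% attrition. The abstract describes the 288 as evaluable.

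**The concern.** A patient found inoperable at reassessment has no surgery and no specimen. Item A, read as written, puts that patient outside the endpoint. Section 2.3.6 puts the same patient in the denominator as a failure. The group is foreseeable, since the protocol itself expects 15–20% to progress and about 30% not to be operated on.

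There is also a gap beside the conflict. The rule in 2.3.6 is triggered by an MRI showing inoperable disease, and 2.3.9 covers only patients spared surgery despite a response. Neither section, nor item A, explicitly gives a value to patients unresected because of distant progression, death or unfitness.

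Following item A literally would condition the primary comparison on reaching surgery. That is a post-randomisation event, decided by a tumour board in an open-label trial, and the study drug could influence it. Blinding the pathologist does not protect against selection into surgery. The phase II result feeds the decision on phase III, so the denominator should not be open to choice once data are in.

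**Working it through.** **Inputs.** 316 randomised, 158 per arm, 288 evaluable (abstract, 2.4). 70% resected, 15–20% progressing (2.4). 15% vs 25% pCR (2.4). Assumptions made here: 70% resected in both arms, and 15% and 25% are rates among resected patients.

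**The plan's own figure.** With pooled variance, n per arm = [z_α√(2p̄q̄) + z_β√(p₁q₁ + p₂q₂)]² / d², where p̄ = 0.20 and d = 0.10.

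- One-sided 0.10: (1.2816 × 0.5657 + 0.8416 × 0.5612)² / 0.01 = 143.4, so 144 per arm and 288 in total.
- Two-sided 0.10, as stated: (1.6449 × 0.5657 + 0.8416 × 0.5612)² / 0.01 = 196.8, so 197 per arm and 394 in total.

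The 288 therefore matches a one-sided 0.10 test, not the stated two-sided one. That is a separate matter. Power is given both ways below so that it does not cloud this point.

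**Patients available.** Resected: 0.70 × 316 = 221. Planned evaluable: 288/316 = 91%. Obtaining 288 resected patients would need 288/0.70, or about 412 randomised.

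**The same data on three denominators.**

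- *(a) Operated patients only (item A as worded):* 15.0% vs 25.0%, 10 points, on about 221 patients.
- *(b) Every unresected patient counted as non-pCR:* 0.70 × 15% = 10.5% and 0.70 × 25% = 17.5%, 7 points, on 316 patients.
- *(c) Sections 2.3.6 and 2.3.9 together*, assuming the inoperable share equals the 15–20% with progressive disease and the remaining 10–15% are left out:
  - 15% inoperable: 10.5/0.85 = 12.4% vs 17.5/0.85 = 20.6%, 8.2 points, on 0.85 × 316 = 269 patients.
  - 20% inoperable: 10.5/0.90 = 11.7% vs 17.5/0.90 = 19.4%, 7.8 points, on 0.90 × 316 = 284 patients.

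**Power with 316 randomised.** Power = Φ{[d√n − z_α√(2p̄q̄)] / √(p₁q₁ + p₂q₂)}.

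| Denominator | n per arm | Two-sided 0.10 | One-sided 0.10 |
|---|---|---|---|
| (a) operated only | 111 | 59% | 72% |
| (b) all unresected as non-pCR | 158 | 56% | 70% |
| (c) 2.3.6 with 2.3.9 | 134–142 | 57% | 70–71% |

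For (a), two-sided: (0.10 × √111 − 1.6449 × 0.5657)/0.5612 = 0.219, and Φ(0.219) = 0.587.

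If 15% and 25% are instead rates over all randomised patients, the operated-only rates become 15/0.70 = 21.4% and 25/0.70 = 35.7%.

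**How conditioning on surgery can mislead (hypothetical).** Take 15 pCRs among 144 patients in each arm, with 70% resected in one arm and 60% in the other. Among operated patients the rates are 15/100.8 = 14.9% and 15/86.4 = 17.4%. Among all randomised they are 10.4% in both. The 2.5-point gap comes only from who reached surgery. No section of the protocol predicts such an imbalance.

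**The case against.** The best defence is that item A defines the event, not the analysis set. On that reading item A says what a pCR is, 2.3.6 says inoperable patients are failures, 2.3.9 says unoperated responders are left out, and the three fit together. The sample size favours this: 288 of 316 evaluable cannot be reached from about 221 resected patients, whereas 2.3.6 with 2.3.9 gives 269 to 284. The reading is plausible, but the article nowhere states it, and item A's words restrict the variable to patients who undergo surgery.

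A second defence concerns the gap. Section 2.3.6 also speaks of patients the tumour board deems inoperable, 2.3.7 refers to inoperable patients without mentioning MRI, and 2.3.4.2 mentions ineligibility for surgery. New metastases might be caught there, and deaths might sit within the 10% attrition. Detailed rules by cause may also be in a full protocol or analysis plan that is not shown. This weakens the gap as a finding in its own right. It does not settle the conflict, because two sections of the same document word the primary endpoint differently for the same patients.

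Two stronger readings are tempting, and neither is supported. A reader might infer that the sections disagree about the whole 30%, and that the effect is 10 or 7 points depending on which is followed. No section counts every unresected patient as non-pCR, and item A and 2.3.9 agree in leaving out unoperated responders. A reader might also infer that the 2.5-point gap above shows bias in this trial. It is an illustration, and it is about half its standard error (roughly 5.4 points with 101 and 86 resected), so it would not by itself decide the test.

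**Conclusion.** The point holds for the inoperable subset. Item A and section 2.3.6 handle those patients differently, and the reading that would reconcile them is not written down. From the operated-only reading to 2.3.6 with 2.3.9, the planned difference falls from 10 points to about 8 (7.8 to 8.2), and the control rate from 15% to about 12%. The 7-point figure is an outer bound. These sizes assume 70% resected in both arms, 15% and 25% as operated-patient rates, and an inoperable share equal to the 15–20% with progressive disease. The last is an assumption about how the 30% divides, not a figure in the protocol.

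Two conclusions do not need that split. Operated patients alone cannot supply 288 evaluable patients from 316 if 70% are resected. The 15% and 25% rates also have no stated denominator. The correction matters because literal use of item A would make the primary comparison depend on a surgery decision taken after randomisation in an open-label trial.

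**What to change.** - Reword 2.5 A so that the primary comparison is not restricted to operated patients. Randomised patients with no resection because of inoperable disease, local or distant progression, death or unfitness before surgery count as non-pCR. Align 2.3.6 with this.
- Reconcile this analysis set with 2.3.9, which drops unoperated responders from phase II. Writing all randomised patients into 2.5 A while 2.3.9 stands would create a new contradiction. Every randomised patient, including one who declines surgery, needs a stated handling.
- Record the reason for no surgery in both arms, and report pCR among operated patients as supportive only.
- State the denominator of the 15% and 25% rates, and restate the power on the denominator chosen.

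The wording, one case record form field and one supportive table cost little. The real cost is a lower headline pCR rate in both arms and, if 15% and 25% are operated-patient rates, lower stated power. At the outer bound this is about 56% with 316 patients at two-sided 0.10 (70% one-sided). Reaching 80% there would take 606 patients (442 one-sided) before attrition. If the planning rates already refer to all randomised patients, counting every unresected patient as non-pCR does not lower the assumed rates.
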